#### 4^th^ assessment visit/post-delivery evaluation

Maternal and neonatal outcomes are collected within 72 h of birth by a research midwife. Infants are weighed at birth (Mobile electronic baby scales, SECA 334, Germany) and detailed anthropometric measurements obtained by research midwives within 72 h of birth including crown-heel length by neonatometer, head, left mid-arm, chest and abdominal circumferences using a lasso tape, and subscapular, triceps and supra-iliac skinfolds by Harpenden calipers (average of 2 measurements, or median of 3 if initial measurements differ by >0.4 mm) [67]. Among consenting participants, infant body compositions are measured by air displacement plethysmography (PEA POD® Cosmed, Illinois, USA) as soon as practical after birth. In these infants, anthropometry is performed at the same time as the PEA POD® measurement. The rest of the birth outcomes are collected from the mothers and the babies’ clinical records.

A short survey is administered to obtain feedback about participation in HUMBA and the study interventions, and the fetal movement questionnaire is repeated.

#### 5^th^ assessment visit (5 months postpartum)

A follow up appointment with the research midwife and a paediatrician are scheduled at 5 months (±2 weeks) postpartum. Maternal lifestyle and food frequency questionnaires, and infant health and well-being questionnaires are completed. Measurements of maternal BP, weight, height, waist and mid-arm circumference, and body composition by Bioelectrical Impedance Analysis [68] (ImpSFB7®, ImpediMed, Brisbane, Australia) are undertaken. Data are collected on infant feeding, allergies, health and anthropometry (weight and length; head, left mid-arm, chest and abdominal circumference; subscapular, triceps and suprailiac skinfolds), and body composition by PEA POD®, if consented. Infant feeding behaviours are assessed using the Baby Eating Behaviour Questionnaire (BEBQ) [69], and infant eating patterns and nutritional intake will be determined by a food frequency questionnaire. Timing of assessment will be based on corrected age. Consent will be obtained for ongoing contact when funding is obtained for further follow up.

### Primary outcomes

The primary maternal outcome is the proportion of women with excessive GWG, defined as mean weekly weight gain >0.22 kg between recruitment and 36 weeks (or weight at the closest gestation to 36 weeks’ if 36 week weight is unavailable) [15].

The primary infant outcome is infant birthweight.

### Secondary outcomes

Maternal secondary outcomes include:Maternal pregnancy glucose metabolism as assessed by OGTT parameters at 26–28 weeks [70], and HbA1c at 28 and 36 weeks and 5 months postpartum.Changes in diet quality and dietary patterns between recruitment, 28–30 weeks and 5 months postpartum [59]Functional health and well-being (SF-12) at 36 weeks and 5 months postpartum [63]Depression and anxiety scores at 36 weeks’ and 5 months postpartum [62, 63]Maternal adiposity at 5 months postpartum (assessed by weight, BMI, waist and arm circumference and fat mass measured by bioimpedance)GDM by NZSSD criteria [66]Pregnancy induced hypertension (preeclampsia and gestational hypertension) [71]Mode of birthBlood lipid concentrations at 28–30 and 36 weeks’ gestation and 5 months postpartumMaternal feedback about participation in the study (survey at post birth visit)

Infant secondary outcomes include:Neonatal anthropometry: head circumference and length, and associated Z-scores [72]; birthweight adjusted for length; girths (chest, arm and abdominal) adjusted for length; subscapular, triceps and suprailiac skin fold thickness adjusted for length; and arm muscle area adjusted for arm lengthNeonatal body composition (via PEA POD®) including fat mass and lean mass adjusted for length and fat mass adjusted for lean massGestational age at birthLGA, by customised [73] and population [72] references.Small for gestational age (SGA, <10^th^ centile), by customised [73] and population [72] references.Admission to neonatal care unit (and reason)Neonatal composite morbidity, including birth trauma (fracture, brachial plexus injury, cephalohaematoma, subgaleal haematoma), hypoxic ischaemic encephalopathy, sepsis, respiratory distress requiring continuous positive airway pressure support, hypoglycaemia requiring dextrose treatment (buccal or intravenous)Initiation and establishment of breast feeding, including feeding in first two postnatal weeks (collected by phone call at 6 weeks and questionnaires)Infant anthropometry and body composition at 5 months of age, as detailed aboveInfant feeding over first 5 months (breast feeding, formula use, complementary feeding with solids)Feeding behaviour as assessed by BEBQ scores [69]Infant Nutritional intake at 5 months, estimated from a four day food frequency questionnaire

Other secondary outcomes include:Attendance at study visitsAdherence to probiotic/placebo regimeCost effectiveness of the intervention

### Sample size and power calculation

A total of 220 participants will be recruited. With 80% power and 100 subjects remaining in each main intervention group (allowing 10% lost to follow-up) we can detect: 25% reduction in excessive GWG from 80% to 60% (based on an 80% rate of excess weight gain in obese participants in the SCOPE study) [16] and 227 g difference in mean birthweight (based on CMH data; mean = 3,638, SD = 521). To allow for the two primary outcomes an alpha of 0.025 has been used for the power calculations (Bonferroni approach).

### Statistical analysis plan

Analyses will follow the principle of intention-to-treat. Participants will be analysed according to the assigned treatment group at randomisation. Statistical models will adjust for the key randomisation stratification variable, BMI at recruitment.

Binary endpoints will be analysed using logistic regression to estimate odds ratios for each of the interventions (dietary intervention and probiotics). Continuous outcomes will be modelled using generalised linear models to estimate any changes in outcomes with the interventions (dietary intervention and probiotics) compared to their respective control groups.

Primary analyses will report marginal effects for each randomised exposure, with adjustment for co-intervention, BMI at recruitment (randomisation stratification variable), ethnicity and sex (infant outcomes). We will also test for interactions between the main effects (primary outcomes only), though this pilot trial has been powered only for the main effects.

Sensitivity analyses will be carried out according to compliance with the study interventions (primary outcomes); specifically these will be:Those women who reported taking their probiotics most of the time at all time points (forgot to take 1–3 per month, or greater than 1 per week but not most days at 28 weeks, 36 weeks and birth visits).Those that attended at least 3 out of the 4 dietary education sessions.

Analyses of secondary outcomes involving maternal data collected at recruitment, 36 weeks’ and 5 months’ will be analysed using mixed methods to allow for the repeated measures of these outcomes over time. Measures of infant body composition (whole-body fat and fat-free mass) will be adjusted by infant sex and ethnicity, and skinfold thickness and arm muscle area will additionally be adjusted for infant length. For birth data, analyses will be adjusted for gestational age at birth (weeks). We will explore for an interaction between intervention effect and infant sex.

For the primary outcomes a two-sided alpha level <0.025 will indicate statistical significance (Bonferroni adjustment). For secondary outcomes, a two-sided alpha level <0.05 will indicate statistical significance.

Depending on the proportion and the pattern of missing data, multiple imputation may be used to impute missing data for some exploratory variables (secondary outcomes).

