#### 1st assessment visit (12^0^ – 17^+6^ weeks)

Confirmation of eligibility, informed consent, and randomisation is conducted at the first assessment visit. Comprehensive information is obtained from the woman and her clinical records, including: demographic, socioeconomic, educational and employment data; medical history; obstetric history such as parity, method of conception, gestation and accuracy of estimated date of delivery, previous pregnancy complications (GDM, hypertensive disease, pre-term delivery, caesarean section); family history of diabetes, hypertension and cardiovascular disease; history of smoking, alcohol and other drug use; medications and nutritional supplements; probiotic food ingestion; maternal anthropometrics: weight, height, waist and mid-arm circumference; blood pressure (BP); finger-prick blood lipid testing (Roche cobas b 101 point-of-care system); samples collection : non-fasting blood and urine specimen for biobank; questionnaires including: New Zealand Food Frequency Questionnaire - Short Form [59], New Zealand Physical Activity Questionnaire [60], Edinburgh Postnatal Depression Scale (EPDS) [61], State-Trait Anxiety Inventory (STAI) [62], and the 12-item Short-Form Health Survey (SF-12) [63]. It takes approximately 30 min to complete these questionnaires.

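### The primary birthweight model leaves out likely prognostic baseline variables that are already collected, and appears to adjust for gestational age at birth, which is measured after randomisation

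*Protocol article*

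**What the plan says.** Infant birthweight is one of two primary outcomes. Under Statistical analysis plan, the primary analyses report marginal effects of each randomised factor "with adjustment for co-intervention, BMI at recruitment (randomisation stratification variable), ethnicity and sex (infant outcomes". Two paragraphs later the same section adds: "For birth data, analyses will be adjusted for gestational age at birth (weeks". That sentence does not say whether it covers the primary birthweight analysis. Gestational age at birth is also listed among the infant outcomes under Secondary outcomes.

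The section on the first assessment visit shows what is recorded at recruitment:
- "obstetric history such as parity, method of conception, gestation and accuracy of estimated date of delivery"
- "maternal anthropometrics: weight, height, waist and mid-arm circumference"
- "history of smoking, alcohol and other drug use"

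Maternal size enters the model only through BMI. The Randomisation section uses BMI in two categories, and the analysis section does not say whether the model uses the categories or the continuous value.

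The sample size section sets the design at "With 80% power and 100 subjects remaining in each main intervention group (allowing 10% lost to follow-up", with an SD of 521 g and a detectable difference of 227 g. It mentions no reduction in variance from covariates.

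**The concern.** Two choices about the same model deserve another look.

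The first concerns efficiency. In a linear model for a continuous outcome, pre-specified prognostic baseline covariates shrink the standard error of the treatment effect without biasing it. They also protect against chance imbalance at about 100 women per group. Parity, height beyond BMI and smoking are plausible candidates, and the data will already be in hand.

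The second concerns what is being estimated. If the birth-data sentence applies to the primary outcome, the model conditions on a variable that the interventions could change. The resulting effect is no longer the total effect on birthweight, because any part acting through earlier or later birth is removed. Where gestational age and birthweight share causes that are not in the model, conditioning can also bias what remains. Baseline terms carry neither problem. For a primary outcome meant to show whether the interventions alter birthweight, this is the weightier half of the point.

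**Working it through.** **Inputs from the document.** SD 521 g, 100 per main-effect group and 80% power (Sample size and power calculation); alpha 0.025 (same section), two-sided (Statistical analysis plan); 1:1 allocation for each factor (Randomisation).

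**Assumed input.** R², the share of birthweight variance explained by added covariates. The document gives no R², correlation or coefficient for any of these variables, so ranges are shown.

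**Step 1: reproduce the stated figure.** Detectable difference = (z₀.₉₈₇₅ + z₀.₈₀) × SD × √(2/n) = (2.241 + 0.842) × 521 × √(2/100) = 227.2 g. Power at 227 g is 79.9% by the normal approximation and 79.4% by the non-central t. The 227 g is therefore right for a two-sided alpha of 0.025 with no covariate adjustment.

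**Step 2: gain measured from the unadjusted SD.** Residual SD = 521 × √(1 − R²).

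| Assumed extra R² | Residual SD (g) | Detectable difference (g) | Power at 227 g | Half-width of 97.5% interval (g) | Equivalent gain in N |
|---|---|---|---|---|---|
| 0 | 521.0 | 227.2 | 79.9% | 165.1 | 0% |
| 0.05 | 507.8 | 221.4 | 82.1% | 161.0 | 5.3% |
| 0.10 | 494.3 | 215.5 | 84.3% | 156.7 | 11.1% |
| 0.15 | 480.3 | 209.4 | 86.4% | 152.3 | 17.6% |

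**Step 3: gain over terms already in the model.** Step 2 starts from a model that adjusts for nothing, which is not the plan. Let the terms already present explain an assumed R₀, and let the added baseline terms explain a partial share of what is left. Residual SD = 521 × √(1 − R₀) × √(1 − partial R²).

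| Assumed R₀ | Partial R² | Detectable difference (g) | Power at 227 g |
|---|---|---|---|
| 0.10 | 0.05 | 215.5 → 210.0 | 84.3% → 86.2% |
| 0.10 | 0.15 | 215.5 → 198.7 | 84.3% → 90.0% |
| 0.30 | 0.03 | 190.1 → 187.2 | 92.5% → 93.3% |
| 0.30 | 0.05 | 190.1 → 185.2 | 92.5% → 93.8% |
| 0.30 | 0.10 | 190.1 → 180.3 | 92.5% → 95.0% |
| 0.30 | 0.15 | 190.1 → 175.2 | 92.5% → 96.0% |

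At R₀ = 0.30 the gain is about 1 to 4 points of power.

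**Step 4: trading gestational age for baseline terms.** Starting again from 521 g and ignoring the other covariates, suppose gestational age alone explains an assumed 20%. Its residual SD is 466.0 g and its detectable difference 203.2 g, against 209.4 to 221.4 g for baseline terms explaining 15 to 5%. If gestational age explains 10% (215.5 g), the trade runs from about 6 g worse to about 6 g better. The swap is therefore not sure to gain precision.

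**Step 5: the effect cited in the Background.** For the 127 g reduction reported there with probiotics, power = Φ(127 / (SD × √0.02) − 2.241). At SD 521 g this is Φ(1.724 − 2.241), about 30%. At R² of 0.05, 0.10 and 0.15 it is about 32%, 34% and 36%.

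**Step 6: gestational age, by setting the passages side by side.** The list of primary adjustments omits it. The birth-data sentence includes it without exempting the primary outcome. The secondary outcomes list treats it as something the interventions may affect. The size of any resulting distortion cannot be calculated from the document.

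**The case against.** The strongest reply is that this is preference. The plan pre-specifies a valid adjusted model that includes the BMI stratifier, and leaving out further baseline predictors of a randomised comparison produces no bias, no inflated Type I error and no contradiction. That stands, so the covariate part is a recommendation to use data already collected, not the correction of an error.

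A reader might go further and infer that the trial is underpowered for birthweight, or that strong predictors have been ignored. The document supports neither inference:
- The 227 g is by construction the difference detectable at 80% power, and it reproduces. Using the unadjusted SD is, if anything, conservative.
- No figure shows that parity, height or smoking predict birthweight strongly in this population.
- BMI already carries part of height and weight, so only body size beyond BMI is missing.
- Step 5 shows that the added terms would not bring a 127 g effect within reach.

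It can also be said that the gestational-age sentence sits in a paragraph that opens with secondary outcomes, so its application to primary birthweight is an inference. That is fair. Birthweight is nevertheless birth data on any ordinary reading, and nothing excludes it, so the ambiguity needs settling in either case.

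Finally, the first-visit section puts data collection and randomisation at the same visit without stating their order, so it should not be claimed that every covariate precedes allocation. Parity and height cannot be altered by allocation in any order; smoking should be taken as status at recruitment.

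**Conclusion.** The point holds as an efficiency recommendation joined to a question of estimand.

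- **Baseline terms.** Their omission costs some precision and nothing else. The gain is modest and rests wholly on an assumed R²: a detectable difference of 221 to 209 g instead of 227 g for an extra 5 to 15% measured from SD 521 g, and about 1 to 4 points of power at 227 g when the model already explains an assumed 30%.
- **Gestational age at birth.** If it is in the primary birthweight model, the analysis no longer estimates the total effect of each intervention and may be biased. This does not depend on any assumed R², but it does depend on reading the birth-data sentence as covering the primary outcome.

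The precision argument is for the linear birthweight model. It does not carry over directly to the logistic model for excessive weight gain, where added covariates change the conditional odds ratio being estimated, so no change is proposed there.

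**What to change.** Before unblinding, amend the analysis wording for primary birthweight as follows:

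1. Add parity, maternal height (together with continuous recruitment BMI or recruitment weight) and smoking at recruitment to co-intervention, the BMI stratification variable, ethnicity and infant sex.
2. State that gestational age at birth is not in the primary birthweight model.
3. Report two sensitivity analyses: the model with gestational age at birth added, and the model with the covariate set now listed.

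The cost is wording and a few degrees of freedom out of about 200; no new data are needed. The real downside is losing from the primary model whatever precision gestational age would have given, which, as step 4 shows, the baseline terms may not fully replace. That is the price of estimating the total effect on birthweight.

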### Study interventions

Dietary intervention vs routine dietary advice Dietary interventionThe multifaceted dietary intervention comprises the following four components.Encounters with nutrition advisorThe nutrition advisors are community health workers (CHW), usually of Pacific or Māori ethnic background, and are experienced in engaging hard-to-reach women in maternity care in our target population. CHW are an integral part of the health workforce in Counties Manukau. They have been trained in the Pacific Heart Beat Certificate of Nutrition by the New Zealand National Heart Foundation, which covers general nutrition as well as complementary extra training in nutrition during pregnancy [51]. A New Zealand registered dietitian has developed a standard operating procedure manual for the CHWs, and provides support, advice and oversight of the nutritional education package administered to participants by the CHWs.The encounters include taking an initial brief diet and physical activity history followed by education on appropriate weight gain and in-depth education on healthy eating. The dietary education includes advice about: portion control, healthy food and drink choices, limiting energy dense foods, healthy recipes, label reading and managing cravings.Each participant has an initial 1–1.5 h educational session (on average at about 14 weeks’ gestation) with the CHW. Three further 30–60 min face-to-face sessions are planned with the CHW at two weekly intervals and be completed by 28 weeks. Compliance with the dietary intervention is being assessed by the number of educational sessions participants attend with the CHW.A HUMBA participant handbook containing detailed information about the suggested content of each of the four dietary education encounter visits is provided to women randomised to the dietary intervention. Participants are also encouraged to use the healthy recipes provided in their handbook.
b)Behaviour change techniquesCHWs have received training in evaluation methodology and counselling techniques, including healthy conversations [52]. Behaviour change techniques are incorporated in the nutrition education sessions including identifying barriers, self-monitoring, goal setting, and providing regular feedback [53]. Targets will be set for optimal GWG at the first visit with the CHW. Weight is measured and plotted on a personalised GWG chart, in the participant handbook, at each subsequent encounter.

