### Assessment of compliance

Compliance with the dietary intervention will be assessed by the number of educational sessions participants attend with the CHW. Compliance with probiotic/placebo will be assessed by the research team via participant self-report at 28 weeks, 36 weeks and birth visits.

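### The dietary compliance analysis can only set self-selected session attenders against all controls, so an inert programme could appear to reduce excessive weight gain

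*Protocol article*

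**What the plan says.** The Statistical analysis plan section of the protocol article makes intention-to-treat the governing principle: "Participants will be analysed according to the assigned treatment group at randomisation". It then adds two compliance-based sensitivity analyses, both on the primary outcomes (excessive GWG and birthweight):

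- **Capsules:** "Those women who reported taking their probiotics most of the time at all time points", explained in parentheses as "forgot to take 1–3 per month, or greater than 1 per week but not most days at 28 weeks, 36 weeks and birth visits".
- **Diet:** "Those that attended at least 3 out of the 4 dietary education sessions".

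No comparator is named for either subset.

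Other sections settle which women could meet each rule.

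- **Diet.** Under Assessment of compliance, "Compliance with the dietary intervention will be assessed by the number of educational sessions participants attend with the CHW". Under Study interventions, the handbook covering "each of the four dietary education encounter visits is provided to women randomised to the dietary intervention". The routine-advice arm receives standard advice and pamphlets, and no sessions are described for it.
- **Capsules.** Under Assessment of compliance, "Compliance with probiotic/placebo will be assessed by the research team via participant self-report at 28 weeks, 36 weeks and birth visits". The Abstract describes probiotic and placebo capsules as identical in packaging and given double-blind.

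**The concern.** Attendance is a behaviour that follows randomisation and is chosen by the participant. Women who keep three or more appointments are likely to differ in prognosis from women who do not. In the dietary arm the rule removes the poor attenders. In the control arm their counterparts cannot be identified and stay in. The two groups then differ for reasons unrelated to treatment.

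There is also a route from outcome to attendance. The dietary sessions after the first include weighing and plotting on a gain chart, and weekly gain from recruitment is the primary maternal outcome. A woman who is gaining quickly might stop coming, or might come more often, so the filter could select partly on the endpoint, in either direction.

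What is at stake is the reading of a secondary layer of evidence. A sensitivity analysis that looks better than the intention-to-treat result is easily taken to mean that the programme works in women who take it up. Here the same pattern could arise from selection alone.

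**Working it through.** **1. The plan's own figure.** Inputs from Sample size and power calculation: 80% vs 60% excessive GWG; 227 g with SD 521 g; two-sided alpha 0.025; 80% power; 100 per main group.

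- GWG: 99 per group are needed (no continuity correction); 100 per group give 80.7% power.
- Birthweight: 101 per group are needed; 100 give 79.9% power. The detectable difference at 100 is 521 × √(2/100) × (2.241 + 0.842) = 227.2 g.

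The stated figure reproduces and the present point does not touch it.

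**2. Which comparison is possible.** Applying the attendance rule to both arms leaves no controls. Applying it to the dietary arm alone leaves attenders against all controls. Against the control group, only the second can be carried out.

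**3. Bias for an inert programme.** Let c be the proportion attending three or more sessions, and let pA and pN be the excessive-GWG rates in would-be attenders and non-attenders, the same in both arms. The control rate is

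p0 = c·pA + (1 − c)·pN,

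so the apparent reduction is

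p0 − pA = (1 − c)(pN − pA).

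**4. Numbers.** p0 = 80% is the protocol's figure. The values of c and the gap are assumptions, because the protocol gives neither. The last column is the chance that a pooled two-proportion test at two-sided 0.025 favours diet (nominal 1.25%), with 100 × c attenders against 100 controls.

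| c | gap (points) | pA | pN | spurious reduction (points) | OR | false benefit |
|---|---|---|---|---|---|---|
| 0.9 | 5 | 79.5% | 84.5% | 0.5 | 0.97 | 1.6% |
| 0.8 | 10 | 78% | 88% | 2.0 | 0.89 | 2.8% |
| 0.6 | 10 | 76% | 86% | 4.0 | 0.79 | 5.3% |
| 0.6 | 20 | 72% | 92% | 8.0 | 0.64 | 14.7% |
| 0.5 | 20 | 70% | 90% | 10.0 | 0.58 | 20.0% |

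Last row: 0.5 × 70% + 0.5 × 90% = 80%; OR = (0.70/0.30)/(0.80/0.20) = 2.333/4 = 0.58. A gap of zero gives no bias. A negative gap makes an inert programme look harmful.

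**5. Simulation check** (200,000 trials, c = 0.6, 72% vs 92%, no treatment effect):

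- intention-to-treat: 0.0 points, false benefit 1.2%;
- filter in one arm only: 8.0 points, 14.6%;
- same filter in both arms: 0.0 points, 1.3%.

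The third line is the case open to the capsule analysis.

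**6. Birthweight.** The same formula applies to means. Assume attenders' babies are 50–200 g lighter and attendance is 50–80%. The bias then runs from (1 − 0.8) × 50 = 10 g to (1 − 0.5) × 200 = 100 g, against a planned 227 g. False benefit runs from 1.7% to 12.9%.

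**7. What the replacement estimates.** With one-sided non-compliance, the complier effect is the intention-to-treat difference divided by c. For illustration, −12 points with c = 0.6 gives −12/0.6 = −20 points. That is right only if assignment does nothing in women below the threshold. If assignment lowered risk by 12 points in every woman whatever her attendance, −20 would overstate the effect by 8 points.

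**The case against.** **These are only sensitivity analyses.** This stands. Intention-to-treat governs, nothing in the protocol gives the compliance subsets decision weight, and the primary conclusion is not at risk. A reader might infer that the trial's main finding is compromised; the document does not support that.

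**The comparator may be left to an unseen analysis plan.** This stands in part. The protocol nevertheless fixes the dietary subset itself, and no choice of control subset can match it, because controls have nothing to attend. Covariate adjustment may narrow the gap but does not restore the randomised comparison.

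**The size is assumed.** This stands. Attendance and the prognosis gap are not in the protocol, and 10 points is the extreme corner of the range shown.

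**The capsule analysis has the same fault.** A reader might infer this, but the documents do not support it. Capsules are identical and blinded, and adherence is collected in both arms. An inert probiotic should be taken as often as placebo, and the same filter in both arms then gives no false benefit. Bias under the null needs a probiotic-only filter, which the protocol neither states nor rules out. If the capsule has real effects on tolerability or outcome, even a two-arm filter can bias, but that differs from an inert product appearing to work.

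**The capsule rule excludes perfect takers and admits women missing 3 of 7 doses.** Read literally, the parenthesis lists only women who forgot doses, but its governing words plainly cover those who never did. This is a wording slip. The 3-of-7 count is not in the protocol; it is the outermost reading, and 4 of 7 taken is still a majority.

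**Requiring reports at every visit selects on gestation and so distorts birthweight.** On a literal reading, women delivering before 36 weeks cannot qualify, although the GWG outcome keeps them through the nearest available weight. The exclusion deserves repair. It produces no false benefit for an inert capsule when both blinded arms are filtered, and the plan also adjusts birth data for gestational age.

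**Conclusion.** The point holds for the dietary subset. Its rule can be met in one arm only, so it replaces a randomised comparison with self-selected attenders against all controls, for both primary outcomes. With an inert programme and the 80% control rate, the spurious reduction in excessive GWG is 0.5 to 10 points under assumed attendance of 50–90% and gaps of 5–20 points. At the upper end that is half of the 20-point effect the trial is powered for. The direction also rests on an assumption: there is no bias if attendance is unrelated to prognosis, and it reverses if attenders have worse prognosis.

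For capsules, what remains is clarification: the protocol does not say that placebo women are filtered too, and the rule's wording literally leaves out never-missers and early deliveries. The planned primary analysis and the sample size need no change.

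**What to change.** **Diet.** Replace the subset with a complier-average causal effect using randomised assignment as the instrument:

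- report a risk difference for excessive GWG and a mean difference for birthweight, with the same covariates as the primary model;
- state the assumption that assignment has no effect in women below the attendance threshold;
- show a second threshold, such as at least one session, because the handbook, the texts continuing to birth and partial attendance all strain that assumption.

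If the subset is kept instead, label it descriptive and non-randomised, and name its comparator.

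**Capsules.** State that the adherence filter applies to probiotic and placebo women alike. Reword the rule so that women who never missed a dose are included. Use the reports available up to delivery, so that women delivering before 36 weeks are not excluded by the rule.

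**Cost.** A few sentences and a little programming on data already planned for collection. The complier-average estimates will have wider intervals than the naive subset.
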